### Safety monitoring

As the administration and dosage of study medications in both anesthesia regimens are within the current clinical practice, we believe that SAEs should be rare. The adverse effects of propofol and remimazolam will be closely monitored during operation by attending anesthesiologists. In case of fetal adverse events, they could stop the infusion of study medications, request the unmaking of group allocation, and inform the principal investigator of any reason for stopping the infusion of study drugs. In addition, a designated investigator will review the occurrence of adverse events possibly caused by study drugs from the start to the end of infusion using chart review. The DMC will perform a review to ensure patient safety. Throughout the study, any adverse events should be reported within 24 h to the DMC.

### Sample size

The primary outcome of this study is the incidence of POD within 5 days after neurovascular surgery. Based on published delirium studies in the neurosurgical population (Harasawa and Mizuno 2014; He et al. 2019; Mokhtari et al. 2020; Morshed et al. 2019; Wang et al. 2020a, 2020b), we estimated the incidence rate and 95% CI as 31.1% (95% CI, 22.9–39.4%). Based on the upper margin of 95% CI, we determined the non-inferiority margin to be 10%. When we plan to enroll an equal number of subjects in each group, a sample size of 330 in each group is needed to detect a difference for a non-inferiority margin of 10%, using a one-sided two-sample *z*-test with unpooled variance, assuming a power of 80%, and a significance level of 2.5%. After considering a drop-out rate of 5%, 348 subjects in each group will be enrolled (a total of 696). The sample size was computed using PASS 2023, version 23.0.1.

Once a patient is enrolled or randomized, the investigators will make every reasonable effort to follow the patients for the entire study period to make the rate of loss-to-follow-up at most 5%. We anticipate high compliance and a low drop-out rate, as all the interventions and sampling in this study will be performed while the patients are under general anesthesia.

### Statistical analysis

All reported study results except adverse events and non-delirium complications are analyzed, following the modified intention-to-treat-principle (ITT). Data will be descriptively presented using summary statistics such as median and quartiles, means and SD, or frequency and percent as appropriate. The standardized mean difference (SMD) will be used for the comparison of baseline data between the randomized groups. Acceptable covariate balance is defined as a standardized mean difference < 0.2 for the entire list of covariates. Repeated measurements, such as NRS score for pain and sleep quality, daily cumulative opioid requirement, and cognitive function will be compared using generalized estimating equation (GEE) analysis among groups.

For the analysis of primary outcome, we will employ a modified ITT principle, which means all randomized participants, regardless of protocol adherence will be included in the primary analysis, except for the case with surgery cancelation and withdrawal of consent after randomization. The incidence among groups will be compared by calculating the 95% CI of the incidence difference: incidence (remimazolam group)-incidence (propofol group), and noninferiority will be achieved if the upper limit of 95% CI is < 10%. The incidence of POD will be compared using a one-sided two-sample *z*-test with an alpha level of 0.025. We will use a multivariable logistic regression model, which will adjust the treatment effect for covariates found to be imbalanced between the two groups.

For the secondary outcome, except for the analysis of intraoperative adverse events and non-delirium complications in which the PP approach will be used, a modified ITT approach will be used. Group comparison will be performed using a two-sample *t* test or Mann–Whitney *U* test as appropriate for continuous variables, and a chi-square test or Fisher’s exact test for categorical variables. We will adjust the effect of imbalanced covariates using a multivariable logistic regression model for count variables and linear regression or quantile regression for continuous variables.

Subgroup analyses will be conducted to assess the consistency of differences in the primary outcome used to differentiate the effect of treatment among different populations (age, sex, surgery type, preoperative cognitive impairment, ASA physical status, duration of anesthesia, alcohol abuse, or preoperative benzodiazepine use within 24 h).

A one-sided *P* value < 0.025 for the primary endpoint and a two-sided *P* value < 0.05 for the secondary endpoints will be considered statistically significant. Missing data will not be replaced, and interim analysis will not be performed. All statistical analyses will be performed by statistical experts utilizing SPSS, SAS, or R software.

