**Fig. 1 Fig1:**
[figure not shown]
The Consolidated Standards of Reporting Trials flow diagram

**Table 1 Tab1:** Overall schedule of participants

Timeline	Enrollment	Allocation	Post-allocation							
Timepoint	Within 72 h of admission	Surgery day	*Postoperative day*							
			*0*	*1*	*2*	*3*	*4*	*5*	*7*	*90*
Enrollment:										
Eligibility screen	X									
Informed consent	X									
Allocation		X								
Interventions:										
Propofol group		X								
Remimazolam group		X								
Assessments:										
Baseline variables	X									
Frailty, fall-down, and functionality assessment	X									X
Cognitive assessment (MoCA)	X								X*	X
Intraoperative data		X	X							
Intraoperative adverse events		﻿X	﻿X							
Delirium assessment (CAM-ICU, 3D-CAM)	X		X	X	X	X	X	X		
Quality of recovery				X						
Pain score and opioid requirement			X	X	X	X	X			
Postoperative neurologic and non-neurologic complications			X	X	X	X	X	X	X	X

^*^If the patient is discharged before POD 7, it is performed before discharge

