#### Secondary outcomes

Secondary outcomes are (1) severity of delirium, (2) number of positive delirium assessment, (3) emergence agitation which is defined as RASS + 1 or more within 30 min after the endotracheal extubation, (4) delayed extubation (> 1 h after surgery), (5) perioperative adverse events including intraoperative awareness with recall or undesirable patient movement, bradycardia with the use of chronotropic agent, laryngeal spasm, bronchospasm, allergic reaction, arrhythmia, cardiac events (myocardial infarction, vasospasm, or cardiac arrest), or massive bleeding, (6) area under the mean blood pressure threshold (AUT), (7) quality of recovery using Qor-15 questionnaire (Stark et al. 2013), (8) postoperative nausea and vomiting (PONV), (9) incidence and severity of non-delirium complications (non-neurologic or neurologic) within 30 days after surgery, which are graded using Clavien-Dindo classification (Dindo et al. 2004; Landriel Ibañez et al. 2011), (10) length of hospital, defined as the number of days from index neurovascular surgery until initial hospital discharge and ICU stay, defined as the number of hours in the neurosurgical ICU following index neurovascular surgery until the initial ICU discharge, (11) changes in cognition. (12) The occurrence of fall-down and associated injury and functionality at 3 months after surgery.

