#### Cognitive function test

Cognitive assessment will be conducted using Montreal Cognitive Assessment (MoCA) at baseline, 7 days after surgery or at discharge whichever comes first, and 3 months after surgery. Mini-mental state examination is the most widely used cognitive assessment tool for screening and diagnosing dementia; however, it lacks the sensitivity and specificity to detect subtle cognitive impairment (Needham et al. 2017). Therefore, we will use MoCA to detect minimal cognitive impairment (Nasreddine et al. 2005). It comprises six domains: Memory; Executive Functioning; Attention; Language; Visuospatial; and Orientation. Three months later, a telephone interview for the cognitive change will be performed using T-MoCA (Pendlebury et al. 2013), which omits visuospatial, executive, and memory functioning from the MoCA test. The occurrence of fall-down and associated injury and functionality using the Barthel ADL index within 3 months will be assessed using telephone interviews.

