#### Postoperative data collection

Pain severity (least and worst) was assessed by NRS from the postoperative day 0 to 5, with 0 (no pain) to 10 (extreme pain). The daily cumulative opioid requirement will be determined from the medical record and quantified using parenteral morphine equivalent (mg) (Ballantyne et al. 2018) until the final delirium assessment is complete. Sleep quality, which is evaluated with the NRS (an 11-point scale where 0 = the worst sleep, and 10 = the best sleep) once daily between 8 and 10 AM) within the 5 days after surgery. The number of valid delirium assessments, along with the reasons why 3D-CAM or CAM-ICU assessments are not conducted, will also be collected.

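### Baseline MoCA has no planned covariate role in the GEE comparison of cognition, so precision that the trial has already paid for is given up

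*Protocol article*

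**What the plan says.** All references are to the protocol article.

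- **Model.** Statistical analysis puts four outcomes under one rule: "Repeated measurements, such as NRS score for pain and sleep quality, daily cumulative opioid requirement, and cognitive function will be compared using generalized estimating equation" analysis among groups. It gives cognition no separate treatment.
- **Cognition visits.** Cognitive function test schedules the MoCA "at baseline, 7 days after surgery or at discharge whichever comes first, and 3 months after surgery". Table 1 places the first of these in the enrollment column, headed "Within 72 h of admission", and allocation in the later surgery-day column. The 3-month test is the telephone version (T-MoCA), which leaves out several domains.
- **The other three outcomes.** Postoperative data collection describes postoperative series only: "Pain severity (least and worst) was assessed by NRS from the postoperative day 0 to 5" for pain, "within the 5 days after surgery" for sleep, and opioid use daily "until the final delirium assessment is complete". Table 1 marks pain and opioid use on postoperative days only.
- **Outcome name.** Secondary outcomes, item 11, is "changes in cognition".
- **Adjustment.** Statistical analysis provides for adjustment of secondary outcomes only for covariates found imbalanced, with acceptable balance defined as a standardized mean difference (SMD) below 0.2. Baseline MoCA is not named as a covariate, and it is not in the lists under Preoperative evaluation and Preoperative data collection.

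**The concern.** A rule that suits series starting after surgery is applied to a series that starts before randomization. A pre-randomization score of the same construct is usually the strongest predictor of the later scores, and its best use is as a covariate. Here it would be adjusted for only if chance made it imbalanced. In the ordinary case it is either subtracted, which brings in its full measurement noise, or not used at all.

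What is at stake is precision on the longer-term counterpart of the delirium question. The Background links delirium to long-lasting cognitive dysfunction, and the test drug is a benzodiazepine. A wider interval makes a modest cognitive harm or benefit harder to see.

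**Working it through.** **Inputs from the article.** Three cognition visits, the first before allocation; 330 evaluable per arm (Sample size); two-sided 0.05 for secondary endpoints; SMD threshold 0.2.

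**Assumptions, because the article gives no MoCA SD, correlation or effect.** Unit SD at each visit, one correlation r between all visits, a common scale, the same true effect d at both postoperative visits, and complete data on 330 per arm.

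**The plan's own figure.** The article states no figure for cognition. Its 330 is for the primary outcome. With n = (1.96 + 0.8416)² × 2p(1 − p) / 0.10², p = 31.1% gives 337 and p = 30% gives 330. 330/0.95 rounds up to 348, as stated. The gap of 7 does not matter here, and 330 is used below.

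**Step 1: how often the stated rule would reach baseline MoCA.** The standard error of a baseline SMD is √(2/330) = 0.078. Then 0.2/0.078 = 2.57, a two-sided probability of about 1%. Even if MoCA is on the list that is checked, it goes unadjusted about 99% of the time.

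**Step 2: variance of the group contrast for the mean of the two postoperative scores** (multiply by 2/330 for the squared standard error).

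- Change from baseline, or group-by-time: (1 + r)/2 + 1 − 2r. This is 0.75 at r = 0.5 and 0.45 at r = 0.7.
- Baseline as covariate: (1 + r)/2 − r². This is 0.50 and 0.36.
- Postoperative scores with baseline unused: (1 + r)/2. This is 0.75 and 0.85.

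The ratio of change to covariate is 0.75/0.50 = 1.50 and 0.45/0.36 = 1.25. In effective sample size, 330 per arm analysed as change is worth 330/1.50 = 220 to 330/1.25 = 264 per arm analysed with adjustment.

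At a single visit the ratio is 2(1 − r)/(1 − r²) = 2/(1 + r), which is 1.33 and 1.18.

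**Step 3: power**, Φ(d/√(2 × variance/330) − 1.96).

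| Contrast | d = 0.20, r = 0.5 | d = 0.20, r = 0.7 | d = 0.15, r = 0.5 | d = 0.15, r = 0.7 |
|---|---|---|---|---|
| Change or group-by-time | 0.843 | 0.969 | 0.604 | 0.819 |
| Baseline as covariate | 0.953 | 0.990 | 0.778 | 0.895 |

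With baseline unused, power at d = 0.20 is 0.843 and 0.796.

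**Step 4: wider range of r at d = 0.20.** At r = 0.3 the change contrast has 71% power against 93% with the covariate. At r = 0.8 the figures are 99.7% against 99.9%.

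**Step 5: check with fitted models.** In 200 simulated trials (r = 0.6, d = 0.20, exchangeable GEE), group-by-time gave a mean estimate of 0.195 with 89% power. Baseline as covariate gave 0.198 with 98%. Both estimates are close to the true value; only precision differs.

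**The case against.** **The article does not spell out the model.** It names no response visits, time terms or contrast, and Data management refers to a predefined statistical plan that is not shown. A GEE on the postoperative scores with baseline as covariate would fit the quoted sentence, and so would a model constrained to equal baseline means, which recovers the precision too. This stands for the unspecified terms: leaving them to the analysis plan is no error. It does not dispose of the point, because the article does state when covariates are adjusted for, and that rule excludes baseline MoCA in nearly every realization of the trial.

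**Change from baseline is a valid analysis.** It is unbiased under randomization, keeps its type I error and matches the outcome as named. This stands. The criticism is of efficiency, not validity.

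**A stronger reading is tempting.** A reader might infer that baseline is one of three response visits under a single group effect. The expected difference at baseline is zero, so the estimate would fall to 2d/3, one third too small. With variance (1 + 2r)/3, power at d = 0.20 would be 55% to 48%. The documents do not support that inference. No sentence makes baseline a response under a group main effect, and an average over baseline and later visits does not estimate change, which is what item 11 names.

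**The figures assume one scale.** The T-MoCA at 3 months will have its own variance and its own correlation with baseline, so the figures are indicative. This stands, but it favours the covariate: a change score needs both tests on one scale, and a covariate does not.

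**Conclusion.** The point holds as a loss of precision. Baseline MoCA is measured in time and is not a planned covariate. Under the likely contrast the comparison stays unbiased, with 1.25 to 1.5 times the variance of a baseline-adjusted one for the mean postoperative score (1.18 to 1.33 times at a single visit). At 0.20 SD and 330 per arm that is 84% to 97% power against 95% to 99%.

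These sizes rest on assumed correlations of 0.5 to 0.7, equal variances, a common scale and complete follow-up. The loss is larger at lower correlation and almost vanishes at 0.8. Shrinkage by one third would arise only if a group main effect over all three visits were tested, which the text does not say. The non-inferiority conclusion on delirium and the total of 696 are untouched.

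**What to change.** In Statistical analysis, take cognition out of the common sentence and give it its own:

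- Responses: the postoperative scores only (day 7 or discharge, and 3 months).
- Terms: group, visit, group-by-visit, and baseline MoCA as a prespecified covariate whatever the observed balance. Let its slope differ by visit, because the 3-month test is the T-MoCA.
- Report: the adjusted group difference with its 95% CI, separately at each of the two visits.

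Keep the existing GEE rule for pain, sleep and opioid use.

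The cost is a sentence or two of text and no new data, since baseline MoCA is already scheduled. The one addition needed is a simple rule, fixed in advance, for patients without a baseline score.

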### Eligibility criteria for participants

Inclusion criteria are (1) patients aged 19 years old or older, (2) ASA physical status classification I to III, (3) elective neurovascular surgery (aneurysm clipping, microvascular decompression, superficial temporal artery to middle cerebral artery bypass, arteriovenous malformation removal, etc.) and receiving general anesthesia.

Exclusion criteria are (1) severe respiratory disease or cardiovascular disease, (2) severe hepatic (Childs-Pugh Score Class C) disease, (3) severe audio-visual impairments that impede communication, (4) hypersensitivity reactions, allergies, or contraindications to the study drugs, (5) evidence of preoperative delirium in Confusion Assessment Method (CAM), and (6) dependency on psychiatric drugs or alcohol.

Dropout criteria are (1) patient withdrawal and (2) surgery cancelation. In participants who withdraw their consent, the reason for their withdrawal will be collected and reported. They will also be asked to specify which aspects of the trial they are withdrawing their consent and participation from. They will be included in the final report of the trial to ensure complete transparency. A participant who withdraws consent for follow-up assessment will be asked about the use of outcome data and only permitted data will be used for the final analysis. All data will be analyzed according to the modified intention to treat (ITT) principle after excluding patients with drop-out criteria.

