### Measurement of outcomes

#### Delirium assessments

Trained investigators who are blinded to the group assignment will assess the development of POD using CAM for the Intensive Care Unit (CAM-ICU) and 3-min diagnostic interview for CAM (3D-CAM) for ICU patients and ward patients, respectively. The assessment will be conducted twice a day from the postoperative day 1 until the postoperative day 5 (or discharge whichever comes first) in the morning and the evening, with at least six hours elapsing between assessments. On the day of surgery, delirium assessment will be conducted at least 2 h after the end of surgery. Delirium will be assessed when patients can be aroused sufficiently (Richmond Agitation-Sedation Scale [RASS] >  − 4) (Scale 2003). 3D-CAM is highly sensitive and specific for delirium in hospitalized patients (Marcantonio et al. 2014) and the CAM-ICU is a well-validated method of delirium assessment in intubated patients or in the ICU (Ely et al. 2001). In addition, we adopted structured chart reviews to prevent missing cases during the night shift to detect episodes of delirium (Inouye et al. 2005; Saczynski et al. 2014). This approach increases the sensitivity while maintaining specificity in detecting the incidence of delirium. The severity of POD will be evaluated using the maximum daily score of the Delirium Rating Scale-Revised (DRS-R-98), 0 (no delirium) to 39 (highest severity of delirium) for patients who are screened positive for delirium based on the 3D-CAM or CAM-ICU.

The type of POD will be classified into 3 subtypes (Peterson et al. 2006), which are hyperactive (with a consistently positive RASS, from + 1 to + 4), hypoactive (with a consistently neutral or negative RASS, from 0 to − 3) and mixed type. The severity of delirium will be assessed in the patients who develop delirium within 5 days using the DRS-R-98 and maximum DRS is used in the analysis, 0 (no delirium) to 39 (highest severity of delirium).

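### The primary analysis set excludes every post-randomization withdrawal, even after an observed delirium event, and this conflicts with the rule that permitted data of withdrawers are used

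*Protocol article*

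**What the plan says.** Three statements in the protocol article decide what happens to a participant who withdraws.

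- **Statistical analysis.** The primary analysis takes all randomized participants whatever their adherence, "except for the case with surgery cancelation and withdrawal of consent after randomization".
- **Eligibility criteria, permitted-data sentence.** A participant who withdraws from follow-up assessment "will be asked about the use of outcome data and only permitted data will be used for the final analysis".
- **Eligibility criteria, drop-out definition and last sentence.** "Dropout criteria are (1) patient withdrawal and (2) surgery cancelation", and "All data will be analyzed according to the modified intention to treat (ITT) principle after excluding patients with drop-out criteria".

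Three further facts bear on the point. Table 1 places allocation on the day of surgery. The primary outcome is any positive assessment from 2 h after surgery to postoperative day 5 or discharge. The Sample size section allows 5% for drop-out and aims to hold loss to follow-up to at most 5% over the whole study period.

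**The concern.** The last sentence of the eligibility section and the statistical section agree with each other: withdrawers are out. The permitted-data sentence says that some of their data are in. The article therefore gives two different primary analysis sets and no rule for choosing between them.

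The exclusion rule has a specific defect. The outcome is met at the first positive assessment, so a patient can have a complete primary outcome on day 1 and then withdraw. The exclusion deletes that observed event. Because allocation falls on the day of surgery and follow-up for the outcome runs for five days, withdrawals after randomization can readily occur after anesthesia.

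At stake is the comparison of randomized groups. If withdrawal is linked to delirium, and more strongly on remimazolam, dropping withdrawers lowers the observed difference and makes the 10-point margin easier to meet.

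**Working it through.** **The plan's own figure.** n per group = (1.960 + 0.842)² × 2p(1 − p) / 0.10², at a true difference of zero.
- p = 0.30 gives 329.7, so 330.
- The stated p = 0.311 gives 336.4, so 337, which is 2.1% above 330.
- 330 / 0.95 = 347.4, so 348 per group and 696 in total, as stated.

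**Inputs for the check**
- From the article: 348 per arm, margin 10 points, one-sided 2.5%, unpooled variance, propofol incidence 31.1%.
- Assumed: a true remimazolam incidence of 41.1%, exactly at the margin; a fraction w withdrawn in each arm after treatment; and the share of withdrawers who are delirious, r_R on remimazolam and r_P on propofol. The documents give none of these.

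**Formulas**
- Rate left after exclusion: p* = (p − w·r) / (1 − w), in each arm.
- Patients left per arm: m = 348(1 − w).
- d = p*_R − p*_P, and SE = √{[p*_R(1 − p*_R) + p*_P(1 − p*_P)] / m}.
- False non-inferiority rate = Φ((0.10 − d)/SE − 1.96).

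**Example: w = 5%, r_R = 0.8, r_P = 0.311**
- p*_R = (0.411 − 0.040)/0.95 = 0.3905, and p*_P stays at 0.311.
- d = 0.0795, m = 330.6, SE = 0.0370.
- Φ(0.0205/0.0370 − 1.96) = Φ(−1.41) = 8.0%.

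**Range**

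| Withdrawn per arm | Delirious among withdrawers, remimazolam | Same, propofol | Observed difference (points) | False non-inferiority rate |
|---|---|---|---|---|
| any | 41.1% | 31.1% | 10.0 | 2.5% |
| 1% | 60% / 80% | 31.1% | 9.8 / 9.6 | 2.8% / 3.2% |
| 2% | 60% / 80% | 31.1% | 9.6 / 9.2 | 3.2% / 4.1% |
| 5% | 60% / 80% | 31.1% | 9.0 / 8.0 | 4.5% / 8.0% |
| 5% | 60% or 80% | same as remimazolam | 10.5 | 1.8% |
| 5% | 41.1% | 80% | 12.6 | 0.4% |

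**Can one result change?** Take 348 per arm with 118 events on remimazolam and 104 on propofol.
- Nobody excluded: difference 4.0 points, SE 3.53, upper limit 4.02 + 1.96 × 3.53 = 10.9. Non-inferiority fails.
- Drop 17 per arm (5%), of whom 10 on remimazolam and 5 on propofol were delirious: 108/331 vs 99/331, difference 2.7, SE 3.60, upper limit 9.8. It passes.
- With 8 instead of 10 on remimazolam: 110/331 vs 99/331, upper limit 10.4. It still fails.

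**The case against.** **The two rules may address different people.** The eligibility section asks withdrawers which aspects of the trial they are leaving, and its permitted-data sentence concerns follow-up assessment. One could read it as keeping partial withdrawers and excluding full ones. That is workable, but neither section states the split, and the drop-out criterion is simply patient withdrawal.

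**The harmful direction needs an asymmetry that no section supports.** This stands. Patients and assessors are blinded, which argues against consent being withdrawn for arm-specific reasons. Equal delirium risk among withdrawers makes the test conservative. Enrichment by the same relative factor in both arms (for example 60% vs 45.4%, or 80% vs 60.5%, at 5% withdrawn) gives only 2.9–3.4%.

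**The full 5% is a ceiling.** This also stands. The allowance covers cancelled surgery as well as withdrawal, and the follow-up target runs over the study period to day 90. Post-treatment withdrawals before day 5 could be far fewer, so the 1–2% rows matter.

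**A stronger reading is tempting.** From "Missing data will not be replaced" and "Delirium will be assessed when patients can be aroused sufficiently", a reader might infer that unassessable patients are deleted or scored delirium-free, that sensitivity analyses are ruled out, and that the plan is built to produce non-inferiority. The documents do not support this. The article does not say how a missed assessment is scored. It assesses patients twice daily from day 1, adds structured chart review, and records the number of valid assessments with reasons for omissions. Not replacing missing data in the main analysis does not bar a sensitivity analysis, and one may stand in the statistical plan that the Data management section mentions and that is not shown.

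**Conclusion.** The point holds as an inconsistency in the definition of the primary analysis set, one side of which discards observed primary events. The statistical section conflicts with one sentence of the eligibility section and agrees with its last sentence, so the eligibility section also contradicts itself.

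The effect on the error rate is conditional. It exceeds 2.5% only if withdrawal is related to delirium and more so on remimazolam: 2.8–4.1% at 1–2% post-treatment withdrawals, and 4.5–8.0% if the whole 5% allowance is of that kind, with propofol withdrawers at their arm average. Under other patterns it is unchanged or lower. Both the withdrawal fractions and the delirium shares are assumptions. The case for correction rests on the conflicting rules and the loss of known outcomes, not on a demonstrated bias toward non-inferiority.

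**What to change.** Reconcile the Eligibility and Statistical analysis sections under one rule.

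- Exclude from the primary set only patients whose surgery is cancelled, who withdraw before study drug is started, or who refuse use of their data.
- Analyse all others as randomized, using every permitted assessment up to withdrawal.
- Count a positive assessment before withdrawal as an event.

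A tipping-point analysis, giving withdrawn or incompletely assessed patients a range of delirium probabilities, is a sensible addition. Its absence from the article is not an error.

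The cost is a few sentences, settled before allocation is opened for analysis, plus one optional sensitivity analysis. No new data are needed: the article already provides for asking withdrawers about use of their data and for recording valid assessments and reasons for missed ones.

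### Chance imbalance, not prognosis, decides which covariates adjust the primary outcome, so precision is forgone; the model named for count outcomes also needs correction

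*Protocol article*

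**What the plan says.** All of this stands in the protocol article under Statistical analysis, unless another section is named.

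- **Primary decision.** Non-inferiority is shown if the upper 95% limit of the incidence difference (remimazolam minus propofol) is below 10%, with a one-sided two-sample z-test at 0.025. No covariate enters this rule.
- **Adjustment of the primary outcome.** The next sentence adds: "We will use a multivariable logistic regression model, which will adjust the treatment effect for covariates found to be imbalanced between the two groups". The threshold is set earlier in the section: "Acceptable covariate balance is defined as a standardized mean difference < 0.2 for the entire list of covariates". The effect measure taken from the model, and its role beside the primary test, are not stated.
- **Secondary outcomes.** Imbalanced covariates are to be handled by a "multivariable logistic regression model for count variables" and by linear or quantile regression for continuous ones. The Secondary outcomes section lists one true count, the "number of positive delirium assessment".
- **Randomization and blinding.** Permuted blocks are used at 1:1, and no stratification factor is named.

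**The concern.** In a properly randomized trial, any baseline difference between arms is due to chance. A rule that admits a covariate only when its observed SMD reaches 0.2 therefore selects on luck. A variable that strongly predicts delirium stays out when it happens to be balanced, while an irrelevant one comes in when it happens not to be. The covariate set is also unknown until the allocation is opened.

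The precision gain from adjustment comes from prognosis, not from imbalance. As the article names no stratification factor, prespecified adjustment is the one route to that gain in the design as described. The article's own subgroup list (age, surgery type, preoperative cognitive impairment, ASA status and others) suggests that candidates exist.

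Two further matters follow from the same sentences. The margin is an absolute difference, whereas a logistic coefficient is a log odds ratio, so the two can be compared only after standardization. And binary logistic regression does not fit a count; cutting the number of positive assessments at any positive would simply repeat the primary endpoint.

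**Working it through.** **Inputs.** From Sample size: 330 evaluable per arm, 348 enrolled per arm, incidence 31.1% (95% CI 22.9 to 39.4%), margin 10 points, one-sided 2.5%, 80% power, unpooled variance. From Statistical analysis: SMD threshold 0.2. Assumed: a list of 20 to 30 baseline covariates (about 19 named items under Preoperative data collection, plus laboratory values, age, sex, ASA class and MoCA), and prognostic R² of 0.05 to 0.20, for which the article gives no figure.

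**1. The plan's sample size.** With true difference 0, n = 2p(1−p)(1.960 + 0.842)² / 0.10².
- p = 0.30 gives 330, the stated figure.
- p = 0.311 gives 337, within 3% of it.
- 330 / 0.95 = 347.4, rounded up to 348, as stated.

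The design basis is therefore reproduced.

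**2. How often the rule is triggered.** Under randomization SE(SMD) ≈ √(2/n).
- n = 330: SE = 0.078; 0.2/0.078 ≈ 2.57; two-sided probability 1.0%.
- n = 348: SE = 0.076; probability 0.8%.
- Simulated binary covariates with prevalence 2 to 50% at n = 330: 0.7 to 1.1%.

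Probability that at least one of k independent covariates reaches 0.2, 1 − (1 − P)^k:

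| k | n = 330 | n = 348 |
|---|---|---|
| 20 | 18.5% | 15.4% |
| 25 | 22.6% | 18.9% |
| 30 | 26.5% | 22.2% |

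A correlation of 0.2 to 0.3 among 25 covariates lowers the 22.6% to about 18 to 21%. A multi-level factor judged by a multivariate SMD is triggered more often: SMD² × n/2 = 0.04 × 165 = 6.6, referred to chi-square with (levels − 1) degrees of freedom, gives 3.7% for three levels, 8.6% for four and 15.9% for five.

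**3. Precision forgone.** Power = Φ(0.10/SE − 1.96), with SE = √[2p(1−p)(1−R²)/330] and p = 0.311.
- R² = 0: SE = 0.0360, power 79.3%.
- R² = 0.05, 0.10, 0.15, 0.20: power 81.3%, 83.3%, 85.3%, 87.3%.

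The gain is therefore 2.0 to 8.0 points. A simulation (330 per arm, 4,000 runs per scenario, one prognostic covariate, logistic model standardized to a risk difference) agrees:

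| R² | Variance cut, always adjusting | Variance cut, SMD rule |
|---|---|---|
| 0.05 | 5% | 0.6% |
| 0.11 | 12% | 1.0% |
| 0.16 | 14% | 1.6% |
| 0.23 | 21% | 1.9% |

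**4. Scale.** Ten points above 31.1% is an odds ratio of (0.411/0.589)/(0.311/0.689) = 1.55. The same odds ratio is 8.6 points at the article's lower limit of 22.9% and 10.7 points at its upper limit of 39.4%. No single odds ratio stands for the margin.

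**5. The count.** Taking one assessment on the day of surgery and two a day for five days (Delirium assessments), the maximum is 1 + 2 × 5 = 11. Fewer are made when discharge comes sooner, so the denominator varies between patients.

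**The case against.** The strongest reply is that nothing here touches the primary conclusion. The decision rule is unadjusted, lies on the margin's own scale and matches the sample-size method. The logistic sentence follows that rule and is not part of it, so declining an optional gain in efficiency is a preference rather than an error. That stands as far as validity goes: a reader might infer that the non-inferiority claim is compromised, and the article does not support that.

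Three other strong readings also go too far.

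- **That adjustment would almost never happen.** This is true of one given two-level or continuous covariate. Over the whole list some adjustment is triggered in a sizeable minority of trials, and more often if surgery type is judged by a multivariate SMD.
- **That the adjusted result is an odds ratio and so useless against the margin.** The article names a model, not an effect measure. A logistic model can be standardized to a risk difference, and an analysis plan that is not shown may say so.
- **That a wrong model was deliberately chosen for counts.** The preceding sentence pairs continuous with categorical outcomes, so count may be a slip for categorical. As printed, though, the wording is wrong for the one true count listed, and categorical outcomes are left without an adjusted model.

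It is also fair that the R² range is assumed and that its low end buys little. What remains is a selection rule that the article states outright, so it is not a detail left to another document, and a better rule costs almost nothing.

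**Conclusion.** The point holds as one of efficiency and clarity, not validity, and the change is worth making. Under the stated rule a given two-level or continuous prognostic covariate is adjusted for about once in 100 trials, whatever its prognostic value. The loss of about 2 to 8 points of power rests on an assumed R² of 0.05 to 0.20, an incidence of 31.1%, 330 evaluable per arm, and the adjusted estimate carrying the primary test. If it is only supportive, the gain is a narrower interval beside an unchanged decision. The 15 to 27% figure rests on an assumed list of 20 to 30 independent covariates, each with the simple two-group SMD.

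The scale point is conditional: without standardization the adjusted result cannot be read against 10 points, and the text does not mention standardization. The wording on count variables needs correction whichever meaning was intended.

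**What to change.** - Drop selection by imbalance and keep SMDs as a description of the arms.
- Prespecify a short list of prognostic baseline covariates, for example age, baseline MoCA, surgery type and ASA class.
- Estimate the adjusted risk difference by standardization from the logistic model, with a robust or bootstrap 95% CI, and compare its upper limit with 10%.
- State before unblinding whether this analysis is primary or supportive.
- Reword the secondary-outcome sentence: logistic regression for binary or categorical outcomes. For the number of positive assessments, use a model that allows for the bound and for the varying number of valid assessments, such as a binomial-type model with overdispersion, or a count model with the log number of valid assessments as offset.

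The cost is wording and standard code. MoCA, surgery type and the number of valid assessments are already collected, and age and ASA class are eligibility items. Making the adjusted estimate primary is the larger step: it changes the primary analysis and should be documented as an amendment. Keeping it supportive avoids that but gives up the gain in power.
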